### Secondary outcome measures

#### Postoperative 1-min walking ability

Physical activity is an important aspect of day-to-day life, and walking capacity is a measure of exercise tolerance that requires muscle strength. Walk tests measure the distance walked over a definite time period, with greater distances indicating better performance [21, 22]. The 1-min walk test will be measured on preoperative day 1, and POD 2, 5, 14, and 30. Participants will be asked to walk as fast as possible around a circular 20-m track over a period of 1 min. Rest breaks will be allowed if required. Walking aids can be used as required. The investigators will continuously assured that the track is consequently followed.

#### Rescue analgesia

Tramadol injection or sustained-release tablets will be used as rescue analgesia whenever patients experience a VAS score ≥ 4 cm. The application time and total amount of rescue analgesia will be recorded postoperatively.

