#### Sample size {14}

The calculation of the sample size was based on previous studies. Ikeuchi et al. [13] reported that the POD 3 VAS scores were 27 ± 16 mm in the steroid group and 43 ± 18 mm in the control group. Kwon et al. [4] reported that POD 3 VAS scores were 35 mm in the steroid group and 41 mm in the control group. We assumed that the mean difference in the VAS score between the high-dose betamethasone group and control group was 0.8, and the mean difference between the normal-dose betamethasone group and control group was 0.4. An estimated standard deviation (SD) of 1.5, significance level (*α*) of 0.05, and power of test (*β*) of 0.8000 will be adopted. Based on the former data, the sample size was calculated as 69 participants per group. Assuming a dropout rate of 10%, the final sample size will be 78 participants per group, and 234 participants will be required for the three groups.

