### Statistical methods

#### Statistical methods for primary and secondary outcomes {20a}

Perioperative outcomes will be summarized using the mean ± SD for continuous variables and the ratio for categorical variables. All statistical analyses will be conducted using the SPSS software (version 13.0. for Windows; SPSS, Inc., Chicago, USA). For continuous variables, the Kolmogorov–Smirnov test will be used to detect the normality of distribution. Analysis of variance (ANOVA) will be used to compare the differences among the three groups, and Dunnett’s *t* test will be conducted to compare the between-group differences. For categorical variables, the chi-square test will be conducted to compare the intragroup differences, and partitions of chi-square methods will be used to compare the between-group differences.

For repeatedly measured outcomes, multivariate analysis for repeated measures ANOVA test will be performed to compare the difference between the three groups, which contains the three intervention groups, time, and group-time interaction. Dunnett’s test will be applied for post hoc comparisons. When the group-time interaction showed a significant difference, a one-way repeated measures ANOVA was conducted to identify the difference in effect between the three intervention groups. The significance level will be set at *α*=0.05. Statistical analyses will be performed by an independent investigator.

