#### Methods in analysis to handle protocol non-adherence and any statistical methods to handle missing data {20c}

An intention-to-treat analysis will be conducted according to the allocation of the original group. If any participant withdraws from the trial, the last observation carried forward method and multiple imputation method will be implemented for missing data adjustment.

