## Discussion

In TKA, an enhanced recovery strategy warrants improved patient comfort during hospital stay and accelerated discharge. Consequently, measures to control pain and accelerate rehabilitation are important. Although the MCPI technique has been proven to be a safe and cost-effective measure, the gold standard for drug combinations has not yet been established. Corticosteroid addition to MCPI is believed to be a key component owing to its local anti-inflammatory effects and ability to reduce the local stress response following surgery. However, there is conflicting evidence regarding its benefits for pain control following TKA. Christensen et al. [18] conducted a randomized controlled trial that compared patients who had MCPI with 40 mg of methylprednisolone or without corticosteroids, and the only significant result was a decreased LOS in the steroid cohort (2.6 vs. 3.5 days). There was no difference in pain scores, ROM, or Knee Society scores at any time point. Chia et al. [17] compared patients who had an MCPI containing high- or low-dose corticosteroid with patients’ MCPI without corticosteroid, and they were unable to find any significant clinical effect on postoperative ROM advantage and pain relief at the two different dosages. In contrast, Seah et al. [16], who used 40 mg of triamcinolone acetate, found a significant reduction in the early postoperative pain scores and lasting increase in the ROM in the steroid group. Wang et al. [10] found that addition of corticosteroids to an analgesic cocktail could prolong the analgesic effects of local anesthetics, reduce inflammation, slightly improve immediate postoperative pain relief, and accelerate recovery in the first 24 h following TKA. They concluded that the additional analgesic effects of corticosteroids were mild and transient, and prospective studies are still needed to determine the best cocktail of periarticular infiltration analgesia. A meta-analysis by Chai et al. [29] demonstrated that cocktail analgesia containing corticosteroid periarticular injection did not contribute to pain relief within 12 h postoperatively; however, from 24 to 72 h, it significantly decreased the pain score at rest and reduced total rescue opioids. A recent meta-analysis by Li et al. [30] demonstrated that adding corticosteroids to multimodal cocktail periarticular injection can relieve the POD 1, POD 2, and POD 3 pain intensity at rest following TKA, with no significant difference in the VAS score at the operation night, POD 4, POD 5, POD 7, and 2 weeks following the operation. Owing to these conflicting results, we plan to design a three-arm, double-blinded randomized controlled trial containing a high or normal dose of corticosteroid MCPI and a noncorticosteroid MCPI to assess their effectiveness in postoperative pain relief, functional improvement, rescue analgesia, and side effects. This study will also provide clinical evidence on the effect of high-dose corticosteroid adjuvant to MCPI on prolonged pain control and better recovery following TKA.

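### If the application time of rescue tramadol means when rescue is given, the only stated route for it (ANOVA with Dunnett) compares rescued patients alone and has little power to show a delay or reduction in rescue

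*Protocol article*

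**What the plan says.** The Rescue analgesia paragraph, under Secondary outcome measures, states that tramadol "will be used as rescue analgesia whenever patients experience a VAS score ≥ 4 cm", and then: "The application time and total amount of rescue analgesia will be recorded postoperatively". It does not say whether application time is the time of the first dose, the time of every dose, or a count of doses.

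Section {20a}, whose heading covers primary and secondary outcomes, summarises continuous variables by mean and SD. It then says "Analysis of variance (ANOVA) will be used to compare the differences among the three groups", with Dunnett's t test for pairwise differences. Its other routes are chi-square for categorical variables, where "partitions of chi-square methods will be used to compare the between-group differences", and repeated-measures ANOVA. No route allows for an event that some patients never have.

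On missing values, section {20c} promises analysis by allocated group and adds: "If any participant withdraws from the trial, the last observation carried forward method and multiple imputation method will be implemented".

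Rescue analgesia is also named in the Abstract and in Objectives {7}. The Abstract's list of indices to be recorded and analysed names rescue consumption, not rescue time.

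**The concern.** A patient whose pain never reaches the rescue threshold has no time of rescue. That patient has not withdrawn, so {20c} supplies no value, and coding the time as 0 h would turn the best result into the worst. Sent down the ANOVA route, the time variable therefore keeps only the patients who were rescued.

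Being rescued is a consequence of treatment. The subsets compared are not the randomised groups, and the patients who did best are left out, probably in unequal numbers by arm. The hypothesis tested becomes equal mean time among those who needed rescue. That says little about whether betamethasone delays or averts rescue, which is what a time of rescue would be expected to show. A steroid that prevents many rescues without shifting the timing of the rest would look inert on this variable.

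**Working it through.** **1. The plan's own figure.** Sample size {14} gives mean differences from control of 0.8 (H) and 0.4 (N), and "An estimated standard deviation (SD) of 1.5, significance level (*α*) of 0.05, and power of test (*β*) of 0.8000 will be adopted". For one-way ANOVA the noncentrality is n × (0.4² + 0² + 0.4²) / 1.5² = n × 0.32 / 2.25. At n = 69 this is 9.81, and power is 0.802; at n = 68 power is 0.795. So 69 per group reproduces. Allowing for 10% dropout, 69 / 0.9 = 76.7, or 77 against the stated 78, a trivial difference. This calculation concerns the pain score; the protocol gives no figure for rescue time. I use 69 per arm below.

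**2. How many patients may have no rescue time.** No rescue rate is given. As a rough gauge, the POD 3 scores cited in {14} are 43 ± 18 mm (control) and 27 ± 16 mm (steroid). By normal approximation the share at or above 40 mm is:
- control: 1 − Φ((40 − 43)/18) = 0.57
- steroid: 1 − Φ((40 − 27)/16) = 0.21

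This is one time point in an outside study, so it shows only that the unrescued share could be large and could differ by arm.

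**3. Simulation, constant effect.** Assumptions: exponential time to first rescue, 72 h window, control share rescued p = 0.50, 0.70 or 0.85, hazard ratio (HR) 0.5 for H against C, √0.5 for N against C, 2,000 trials per scenario. The share rescued in H is 1 − (1 − p)^0.5.
- ANOVA route: H against C among rescued patients, variance pooled over three groups, critical value 2.23 (Dunnett, two comparisons).
- Alternative: log-rank H against C on all 69 + 69 patients, same critical value.

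| Control rescued | H rescued | Rescued-only test finds benefit | Log-rank, all patients |
|---|---|---|---|
| 50% | 29% | 4% | 62% |
| 70% | 45% | 8% | 81% |
| 85% | 61% | 18% | 90% |

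With no effect, each test rejects in about 1 to 2% of trials per direction, so the gap is not a matter of test size.

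**4. Other assumed rates (three-group tests).** Rescued shares C/N/H were 80/65/50, 60/45/30, 58/47/37 and 57/39/21%.
- Proportional hazards over 72 h: rescued-only ANOVA rejects in 7 to 17% of trials, log-rank in 63 to 99%.
- A 30-day window with 60/45/30%: 8% against 93%.
- Rescue prevented but timing unchanged among the rescued: 5 to 6%, the nominal level, against 59 to 98%.

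**5. Dependence on when the effect occurs.** Control rescued 50/70/85%, H against C:

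| Effect on rescue hazard | Rescued-only test significant in the wrong direction |
|---|---|
| None before 24 h, HR 0.3 after | 24 / 25 / 20% |
| None before 24 h, HR 0.5 after | 10 / 9 / 6% |
| None before 12 h, HR 0.5 after | 5 / 4 / 1% |
| HR 0.7 before 24 h, 0.5 after | 2 / 1 / 1% |
| HR 0.5 throughout | under 1% |

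In the first row, mean time among the rescued is 5 to 9 h shorter under steroid, and log-rank finds the benefit in 42 / 51 / 46%. Conversely, with HR 0.5 before 24 h and none after, the rescued-only test does better than log-rank: 15 / 26 / 39% against 11 / 16 / 27%.

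**6. Total amount.** With 0 for unrescued patients, ANOVA on total amount kept 44 to 93% power in the scenarios of step 4 and in variants where only late rescue is prevented. The amount distribution is also an assumption.

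**The case against.** The strongest reply is that the protocol never says rescue times are compared by ANOVA or that unrescued patients are dropped. The time is to be recorded; the Abstract lists only consumption for analysis; and a condensed article may leave such detail to an analysis plan that is not shown. This stands in part. The ANOVA comparison is inferred from the general rule in {20a}, and the absence of a censoring rule would not by itself be a finding. But the time is part of a listed secondary outcome, {20a} claims to cover secondary outcomes, and the one rule it gives for such a variable does not suit it.

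Second, the term is ambiguous. If it means number of applications, every patient has a value and the concern disappears. This stands, and the point is conditional on the timing reading. Timing is the more natural sense beside a total amount, but the text does not settle it.

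Third, a reader might infer that the trial would miss a sparing effect altogether. The documents do not support that. Total amount is in the same sentence and is defined for all patients, and a rescued yes/no comparison would fit the chi-square route.

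Fourth, a reader might infer that the test will report steroid as bringing rescue forward. The Discussion cites a meta-analysis in which corticosteroid "did not contribute to pain relief within 12 h postoperatively; however, from 24 to 72 h, it significantly decreased the pain score at rest", but that concerns pain at rest, not rescue. The same section cites a study reporting slightly better immediate relief and faster recovery in the first 24 h, and a second meta-analysis with benefit from POD 1. Step 5 shows that a reversal needs an effect confined mainly to late rescue, and that an effect confined to the first 24 h favours the rescued-only test.

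**Conclusion.** The concern holds in a limited, conditional form. If application time means when rescue is given, the stated route for continuous outcomes restricts the comparison to patients selected after randomisation by an effect of treatment. Under a constant HR of 0.5 it detects the benefit in about 4 to 18% of trials, against about 62 to 90% for log-rank on everyone. These figures rest on assumed rescue rates, an exponential model and a 72 h window; the other rates and the 30-day window in step 4 agree in direction.

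A wrong-direction result is possible but depends on a mainly late effect, which the Discussion leaves open. The point is confined to the timing component of one secondary outcome. It does not show that the trial would fail to detect a sparing effect, and the primary VAS conclusion is not affected. The change is worth making because rescue analgesia is a stated objective and the correction is cheap.

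**What to change.** - **Rescue analgesia:** state that application time means time from end of surgery to first rescue tramadol. If number of applications is meant, say so and enter 0 for unrescued patients; the changes to the time analysis are then not needed.
- **Section {20a}:** take time to first rescue out of the ANOVA route. Analyse all randomised patients with Kaplan-Meier curves and a log-rank or Cox comparison of H with C and N with C, using the same two-comparison adjustment. Censor unrescued patients at end of follow-up or at withdrawal.
- **Reporting:** give the proportion rescued by arm, and analyse total amount in all patients with 0 for those not rescued.

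The cost is a few sentences. The times are already to be recorded, SPSS has the procedures, and no clinical rule changes. The small downside is that this outcome appears as curves and hazard ratios instead of mean and SD.

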#### Other outcomes

The circumference of the knee has been shown to have acceptable reliability for the determination of gross changes in knee swelling and inflammatory status in patients post-surgery [23]. Knee swelling will be measured using the circumference of the knee at the mid-portion of the patella with the knee in full extension. Measurements will subsequently be taken 10 cm proximal to the superior pole of the patella (thigh) and 10 cm distal to the inferior pole of the patella (calf). The skin will be marked at these points, and the tape measure will be placed circumferentially around the limb. The circumference at the three measurement positions will be measured on preoperative days 1, 2, 5, 14, and 30. The Knee Society Score will be applied to evaluate knee function on preoperative days 1, and POD 14 and 30.

Perioperative changes in serum CRP, interleukin 6 (IL-6), erythrocyte sedimentation rate (ESR), and blood glucose (Glu) will be analyzed on POD 2, 5, 14, and 30.

#### Adverse event

Adverse events during the trial include serious adverse events (SAEs) and common adverse events. SAE in TKA is defined to cause serious results that required surgical treatment or intensive treatment during the first 3 months following TKA [24, 25]. Common adverse events are minor operation-related complications requiring additional care, but little threat to the patients’ life [25–28]. A brief description of adverse events is summarized in Supplementary Table 1. It should be noted that all hospital adverse events in each patient will be collected. The total occurrence rate of common adverse events will be analyzed and defined as the presence (yes) or not (no) of any event within the entire trial. For example, if a patient experienced postoperative anemia, nausea, and hypertension during hospitalization, he or she will be counted for a “yes” only once. Moreover, if a patient only experienced vomiting one time, he or she will likewise be counted for a “yes.” This will also be applied to the computation and analysis of SAE.

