#### Provisions for post-trial care {30}

As a routine follow-up plan, participants are advised for clinic follow-up visits at 2 weeks, 4 weeks, 8 weeks, and 3 months; the investigators (CZ and LZ) will contact the participants for routine clinical follow-up as post-trial care. Previous studies on the intravenous use of corticosteroids have shown that postoperative blood glucose rise, gastrointestinal ulcers, and poor wound healing could occur. In this study, the topical use of corticosteroids may have similar risks during the trial. These adverse events are included in the common adverse events of TKA and will be covered by the government health care insurance.

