#### Adverse event reporting and harms {22}

All SAEs will be recorded in the medical records and case report forms, including the onset date, complete description of the event, severity, duration, action taken, and outcome. The chief investigator will complete the SAE form, and the form will be emailed to the ethics committee of The Second Affiliated Hospital within five working days of awareness of the event. The chief investigator will respond to any SAE queries raised by the ethics committee as soon as possible. All common adverse events will be recorded on the case report forms.

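### The SAE definition turns on the treatment given, so a death or a serious medically managed event may fit neither adverse event class, and an unconditional common label for steroid risks adds to the ambiguity

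*Protocol article*

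**What the plan says.** All references are to the protocol article.

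- **Adverse event section, classes.** There are two: "Adverse events during the trial include serious adverse events (SAEs) and common adverse events".
- **Same section, SAE.** "SAE in TKA is defined to cause serious results that required surgical treatment or intensive treatment during the first 3 months following TKA". Death, threat to life, a new or longer hospital stay and lasting disability are not mentioned. What counts as intensive treatment is not stated.
- **Same section, common events.** "Common adverse events are minor operation-related complications requiring additional care, but little threat to the patients’ life".
- **Same section, list and collection.** "A brief description of adverse events is summarized in Supplementary Table 1"; that table is not available here. Collection does not depend on class: "It should be noted that all hospital adverse events in each patient will be collected".
- **Same section, counting.** The common-event outcome is one yes or no per patient over the trial, and a single episode of vomiting is enough for a yes. For serious events: "This will also be applied to the computation and analysis of SAE".
- **Provisions for post-trial care {30}.** The section names glucose rise, gastrointestinal ulcers and poor wound healing as corticosteroid risks. It then says: "These adverse events are included in the common adverse events of TKA". The sentence goes on to insurance cover and sets no severity limit.
- **Adverse event reporting and harms {22}.** The chief investigator completes a form for each SAE, and "the form will be emailed to the ethics committee of The Second Affiliated Hospital within five working days of awareness of the event". Common events go on the case report form.
- **Sections {11b} and {17b}.** A reported SAE is the stated occasion for the chief investigator to consider ending the trial for a participant. Unblinding is limited to an SAE or an emergency rescue.

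**The concern.** A two-class scheme works only if every event falls into exactly one class. Here one class is defined by the treatment received and the other by the event being minor. These are not complements: an event can be grave without having led to surgery or intensive treatment. Separately, three named steroid risks are given a class by type, although the definitions go by treatment and gravity.

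The class has consequences. It decides whether the ethics committee receives a form within five working days, and it bears on unblinding and on ending participation. It also decides which of two yes/no safety outcomes the event enters. A serious event recorded as common may be absorbed, because a patient who already has a yes for nausea or vomiting adds nothing further.

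Adverse events are among the stated objectives, and the arms differ only in betamethasone (21 mg, 7 mg, none). The harms that the protocol itself links to corticosteroids are among those whose class is unclear.

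**Working it through.** No figure in the article bears on this point, so the check is a reading of the definitions against example events. The inputs are the two definitions in the Adverse event section and the label in the post-trial care section {30}. The examples are illustrations and are not predicted by the protocol.

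| Example event | SAE definition met? | Common definition met? | Label in {30} | Resulting class |
|---|---|---|---|---|
| Death with no surgery or intensive treatment beforehand | No | No: not minor, not of little threat to life | None | Neither |
| Serious infection treated medically on an ordinary ward | Only if intensive treatment is read broadly | No: not minor | None | Neither, or SAE on the broad reading |
| Serious gastrointestinal ulcer treated medically | Only if intensive treatment is read broadly | No: not minor | Common | Common by label only, or SAE in conflict with the label |
| Poor wound healing with a serious result needing surgery | Yes | No: not minor | Common | SAE by definition; the label disagrees |
| Mild, brief glucose rise needing extra care | No | Yes | Common | Common; no difficulty |

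1. *The classes are not exhaustive.* The first row fits neither class on the printed wording. The second row depends on a term that the article does not define.
2. *The steroid-risk label does not follow the definitions.* In the third row the label is the only text that assigns a class on the narrow reading, and it assigns common to an event that the common definition excludes. In the fourth row the definition yields an SAE, but the label carries no condition that says so.
3. *The class carries through.* Under {22} only the SAE class leads to the five-working-day form. Under the counting rule, each class feeds its own yes/no outcome per patient. An event in neither class has no stated reporting route and no stated outcome. An event filed as common has the case report form and the common-event outcome.
4. *Minor events are unaffected.* The last row shows that the problem concerns serious events, not every instance of the three named risks.

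**The case against.** The strongest reply has four parts.

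*The post-trial care sentence is about insurance cover, not classification.* This is largely right. A reader might infer that steroid harms stay common even when they need surgery. The documents do not say so. The Adverse event section is the defining one, and applied as written it makes a wound problem with a serious result taken to surgery an SAE. What stands is that the label has no severity condition and so sits badly with that section once such an event is serious.

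*Nothing goes uncollected or unseen.* A reader might also infer that SAE counts and ethics committee reports will miss these events. That too is more than the documents support. All hospital events are collected and common events are analysed. Blood glucose is measured on postoperative days 2, 5, 14 and 30, so a glucose difference between arms does not depend on the event class. The steering committee reviews safety data {21b}, ethics committee staff sit on the data monitoring committee {21a}, and the ethics committee meets monthly to review conduct {23}. Unblinding is open for emergency rescue as well. What stands is that collecting an event does not classify it, an event outside hospital may not count as a hospital event, and periodic review is not the five-working-day form.

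*Intensive treatment may be meant broadly.* It may, and then many medically managed serious events would be SAEs. A death that received no treatment would still fall outside, and the rest would depend on each investigator's reading.

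*Supplementary Table 1 may settle it.* It may list death or specific events by class and so narrow the gap. Its absence here is not a fault of the plan. A list by diagnosis would help, but the definitions in the text would still need to agree with it.

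**Conclusion.** The point holds as a defect of wording with safety consequences. As printed, the SAE definition depends on treatment given, omits death and other grave outcomes, and is not the complement of the common class. The unconditional label on the three steroid risks conflicts with it for serious cases. Deaths without surgery or intensive treatment, and serious events managed medically, may therefore be left out of the SAE comparison and of expedited reporting.

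No numerical size is given. The article states no expected SAE rate, and any count of misfiled events would be a guess. The conclusion assumes that investigators apply the definitions literally and that Supplementary Table 1 does not already assign these events. It does not assume that events go unrecorded, and it does not bear on the pain outcome or the sample size.

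**What to change.** - **Adverse event section, SAE.** Define an SAE by outcome: any event that causes death, is life-threatening, needs or prolongs a hospital stay, leaves lasting disability, or needs surgical or intensive treatment. Apply this regardless of diagnosis or presumed cause, and say what intensive treatment covers.
- **Same section, common events.** Define these as all adverse events that meet no SAE criterion, so that each event has exactly one class.
- **Section {30}.** State that glucose rise, gastrointestinal ulcer and poor wound healing are common adverse events only when no SAE criterion is met.
- **Consistency.** Check Supplementary Table 1, the case report form and section {22} against the revised definitions.

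The cost is rewording in the protocol and the case report form, and somewhat more SAE forms for the chief investigator and the ethics committee. Recruitment has begun, so events already recorded should be reclassified, blind to allocation, under the same definitions. No dose, treatment or visit changes.

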### Trial design {8}

This is a protocol for a three-arm, randomized, placebo-controlled trial (Fig. 1). It will follow the recommendations and suggestions of the Consolidated Standards of Reporting Trials (CONSORT 2010). The study will be conducted at a 4-week follow-up. Eligible participants will be randomized in a 1:1:1 ratio for enrollment in one of the three groups to receive a high dose of betamethasone MCPI (group H), normal dose of betamethasone MCPI (group N), and non-betamethasone MCPI (group C).

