#### Criteria for discontinuing or modifying allocated interventions {11b}

Participants are permitted to withdraw from the study at any time without consequence. When serious adverse events are reported during the trial, either participant is able to make a withdrawal request or the chief investigator can consider to cease the trial for the participant.

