### Outcomes {12}

#### Primary outcome measures

The primary outcome will be knee pain during 90° flexion via VAS pain score measured by a 10-cm horizontal line scale [19]. The patients will be asked, “How much pain do you have this moment?”, the patient will then mark on the 10-cm horizontal line VAS. Zero means “absence of pain,” while 10 represents “the worst pain” VAS has been proven to be a valid and reliable outcome measure for recording pain with ICC = 0.96 to 0.98, according to a previous study [20]. The VAS score will be evaluated at preoperative day 1; postoperative 6, 24, 48, and 72 h; day 5; day 14; and day 30 following the surgery.

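### Serious adverse events are defined over 3 months in a 4-week trial, and reoperation or knee trauma during the study is listed as an exclusion despite intention-to-treat

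*Protocol article*

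**What the plan says.** **SAE window.** Under Adverse event, an SAE is an event that "required surgical treatment or intensive treatment during the first 3 months following TKA". The same section says that "all hospital adverse events in each patient will be collected". It analyses common events as a per-patient indicator, "defined as the presence (yes) or not (no) of any event within the entire trial", and applies the same rule to SAEs.

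**Length of the trial.** Trial design {8} says: "The study will be conducted at a 4-week follow-up". The primary outcome is measured at "postoperative 6, 24, 48, and 72 h; day 5; day 14; and day 30 following the surgery". No secondary or other outcome is scheduled later than day 30.

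**Visits after day 30.** Provisions for post-trial care {30} states that "participants are advised for clinic follow-up visits at 2 weeks, 4 weeks, 8 weeks, and 3 months" and describes the contact as routine care after the trial. The section on retention and complete follow-up {18b} lists the same four visits, this time as a means of completing follow-up.

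**Exclusions and analysis set.** The last exclusion criterion combines earlier major knee surgery with reoperation and with knee trauma in the course of the study. Section {20c} states: "An intention-to-treat analysis will be conducted according to the allocation of the original group".

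**After an SAE.** Section {11b} lets the participant ask to withdraw and adds that "the chief investigator can consider to cease the trial for the participant". Section {22} requires every SAE to be entered in the medical record and the case report form.

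**The concern.** Adverse events are a stated objective, and the protocol itself names poor wound healing among the possible risks of the steroid. The safety comparison therefore needs one clear rule on which events count and in which patients. The text gives two rules on each.

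First, the definition runs to 3 months while the counting period is the trial, which is stated to last 4 weeks. Two teams following this protocol could report different SAE rates from the same patients: one stops at day 30, the other includes what is found at the 8-week and 3-month visits.

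Secondly, an event that happens during the study cannot be screened for at entry. If a patient who is reoperated on, or injures the knee, is excluded as the criterion says, the randomised groups are altered by something that happened after allocation. For reoperation, the excluded patient can be the very patient who had the SAE.

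**Working it through.** The protocol derives no SAE figure, so there is none to reproduce. The check compares the passages and the lengths of the two periods.

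**1. Share of the SAE window inside the trial.** Inputs: 3 months, taken as 90 days (Adverse event); 4 weeks = 28 days (Trial design {8}); last assessment on day 30 (Primary outcome measures).

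- To 4 weeks: 28/90 = 31% covered, (90 − 28)/90 = 69% not covered.
- To day 30: 30/90 = 33% covered, (90 − 30)/90 = 67% not covered.

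About two thirds of the defined window lies after the last scheduled assessment. This is a share of calendar time, not of events.

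**2. Do the later visits close the gap?** The 8-week and 3-month visits span the rest of the window.

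- Under {18b} they serve complete follow-up. If SAEs found there enter the trial record, nothing is lost.
- Under {30} they are care after the trial. An SAE first seen there falls outside the counting period.

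Nothing in the article says which reading governs. The description of collection as concerning hospital events adds to the doubt.

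**3. What a gap could mean in numbers.** The document gives neither an SAE rate nor a distribution over time, so this is an illustration under assumptions. Assume a 3-month SAE risk of 5%. With 78 patients per arm (Sample size {14}), the expected number is 78 × 0.05 = 3.9 per arm. If a share f occurs after day 30 and none of these is collected, the number counted is 3.9 × (1 − f):

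| f | Counted per arm |
|---|---|
| 10% | 3.5 |
| 20% | 3.1 |
| 33% | 2.6 |
| 50% | 2.0 |
| 67% | 1.3 |

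If the later visits do feed the SAE record, the count stays at 3.9 throughout.

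**4. The exclusion against the analysis rule.** Allocation takes effect in the operating theatre: the envelope is opened after anaesthesia ({16c}), and the injection is given before wound closure. A reoperation during the study therefore comes after randomisation. The eligibility text says that participants meeting a criterion are excluded; {20c} says that patients are analysed as allocated. Both cannot be followed for the same patient. A reoperation is surgical treatment and, within 3 months, can meet the SAE definition. Knee trauma meets it only if it leads to surgical or intensive treatment.

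**5. Ending participation after an SAE.** The rule in {11b} is optional and takes effect once an SAE has been reported. By then {22} has the event on the case report form, and the yes/no count for that patient is fixed. Only later outcomes and later common events in that patient are at risk.

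**The case against.** The strongest reply is that nothing shows any event will be lost. Section {22} records all SAEs, {18b} schedules visits to 3 months under complete follow-up, and {20c} keeps every patient in the allocated arm. The schedule figure and the supplementary adverse event table are not available here and might settle the SAE period. Much of this stands: the defect is conflicting text, and an under-count is possible rather than demonstrated. But recording an SAE is not the same as including it in a comparison restricted to the trial period, and nothing says whether {20c} or the exclusion list prevails.

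One could also read the phrase about the study period as governing trauma only, with reoperation meaning past surgery. A post-baseline exclusion for trauma would still remain.

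A reader might go further, in three ways that the documents do not support:

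- *Steroid harms will be under-counted in favour of the high-dose arm.* The rules apply to all arms, and no SAE rate, timing or arm difference is given. Neither the direction nor the size of a bias can be derived, for safety or for efficacy.
- *The optional withdrawal rule loses the SAE itself.* It does not, as step 5 of the working shows.
- *The glycaemic exclusion removes patients whose glucose rises after the injection.* That depends on one reading of the word perioperative. The criterion stands beside diabetes in an eligibility list, where a screening reading is natural, and glucose as an outcome is measured within the 30-day schedule.

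**Conclusion.** The point holds as two contradictions that should be resolved before the safety analysis.

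1. The SAE definition covers 3 months, while the counting period is a trial of 4 weeks. The visits that could cover the difference have an unclear status. SAEs in about two thirds of the window (67% from day 30, 69% from day 28, taking 3 months as 90 days) may not enter the comparison by arm.
2. Excluding patients for reoperation or knee trauma during the study conflicts with intention-to-treat and, for reoperation, could take patients with an SAE out of the SAE comparison.

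The number of events affected and any imbalance between arms cannot be derived from the document. The counts in step 3 rest on an assumed 5% risk and show only that, with about four expected events per arm, a few missing ones would matter.

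**What to change.** - Set one SAE collection period, to 3 months after surgery. State that the 8-week and 3-month visits supply it, make the wording of Trial design {8}, Adverse event, {18b} and {30} agree, and report SAEs by randomised arm.
- Remove reoperation and knee trauma after randomisation from the exclusion criteria, and keep these patients in the intention-to-treat set. Record the event as an SAE where it meets the protocol's definition, and otherwise as a common adverse event.
- State in {11b} that outcome and adverse event collection continues after an SAE unless the patient withdraws consent.

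The cost is a wording amendment, notified as the protocol's own amendment section requires since recruitment has begun, and SAE forms at two visits that are already planned. Final safety data would come about two months later. The pain analysis and the sample size are not affected.
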